#### Service context questionnaire

The service context questionnaire, stakeholder information sheet and a consent form will be emailed to the Primary Health Care Manager or equivalent in the intervention sites (*n* = 6) to complete. A follow up interview will be conducted the health service managers to explore any missing information and confirm the responses to the questionnaire. The completed questionnaires will be transcribed, collated and coded using nVivo.

#### Scoring model components

A directed acyclic graph (Fig. 2) illustrates the measures proposed to assess implementation fidelity and map to the dimensions of adherence, dose, quality, and responsiveness. Some measures will be dichotomous (i.e yes or no) while others will be assigned a percentage score based on the level of implementation that occurred. Per protocol analysis will be followed when determining compliance. A weighting for each element will be assigned to reflect the importance of the element. It is expected that additional criteria will need to be developed to define compliance. A workshop will be held with key stakeholders to validate the scoring process and agree on weightings that should be applied to different model components, for each dimension.

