## Methods/design

The aim of this study is to adapt the implementation fidelity framework developed by Keith et al. and apply it to the communities that participated in phase 1 of the Getting Better at Chronic Care in North Queensland (GBACC) study. The GBACC study was a cluster randomised control trial (RCT)of intensive case management by Indigenous Health Workers of people with complex chronic disease care needs [26]. The primary outcome measure was reduction in HbA1c over 18 month and there were a range of secondary measures including improvement in clinical process measures and hospital avoidance for ambulatory sensitive chronic conditions. The study produced modest results and a possible reason for this is implementation failure of the intervention. This study will quantify the level of implementation fidelity achieved during phase 1 of the GBACC study and investigate the features of the primary health care system that contributed to successful improvement in clinical measures and hospital avoidance for ambulatory sensitive conditions.

The objectives of the study are to:Investigate the features of primary health care service models that contribute to intervention effectiveness for chronic disease care of Indigenous patients and identify if they are present in the context of health services participating in the GBACC study.Assess the level of implementation fidelity achieved for each component of the intervention in each community.Measure the level of implementation fidelity achieved in each communityDetermine if there is any association between implementation fidelity and health outcomes as measured by HbA1c and preventable hospitalisation for diabetes related conditions for communities in the GBACC study.

The study has approval from the Far North Queensland Human Resource Ethics Committee (HREC), University of Queensland HREC and the University of South Australia HREC.

A convergent parallel mixed methods design will be used to develop the measures for assessing implementation fidelity for each component of the intervention implemented during phase 1 of the study. The study will be executed in three stages using a model adapted from Carrol (2007 and Keith (2010). The analysis will use routine data generated by the GBACC study, clinical data collected to measure the outcome from the RCT and additional information collected via a questionnaire to describe the health service context in which the study occurred. The model is illustrated in Fig. 1.

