#### Development of measures for implementation fidelity

The GBACC model of care (the intervention), the theory underpinning the model and each component of the model was documented during phase 3 of the GBACC study. The description of the model and the measures for assessing each component and the data sources proposed to assess implementation of each component were discussed with stakeholders at a workshop in May 2015. Modifications were made to the description of the component and consensus achieved on measures to be used to assess implementation fidelity of the GBACC study.

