**Fig. 2 Fig2:**
[figure not shown]
Directed Acyclic Graph (DAG) - Implementation fidelity GBACC project

A series of excel tables will be generated that shows the raw data and implementation score assigned for each component. All model components will be aggregated by community to develop an implementation fidelity score for each community.

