### Stage 3: Assessment of intervention effectiveness

The objective of stage 3 is to assess the impact of the program by looking at the association between the implementation fidelity score and outcome effectiveness. The aim is to determine if it is possible to predict outcome effectiveness based on the features of the PHC system. Intervention effectiveness (i.e implementation fidelity score for each component) is the independent variable and avoidable hospitalisations and service utilisation is the dependent variable.

Figure 3 provides a summary of the study design to assess implementation fidelity of phase 1 of the GBACC study.

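### Component weights and further compliance criteria are still to be set after the trial's overall result is known, so the fidelity score could be shaped by the outcomes it is then compared with

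*Protocol article*

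**What the plan says.** The Methods/design section describes the cluster trial as finished and gives a favoured explanation of its result: "The study produced modest results and a possible reason for this is implementation failure of the intervention". The fidelity study will reuse that trial's data, including "clinical data collected to measure the outcome from the RCT".

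Under Development of measures for implementation fidelity, a stakeholder workshop in May 2015 is reported in the past tense, with "consensus achieved on measures to be used to assess implementation fidelity of the GBACC study".

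Under Scoring model components (Stage 2), the rest of the scoring rule lies in the future:

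- On weights: "A weighting for each element will be assigned to reflect the importance of the element".
- On compliance: "It is expected that additional criteria will need to be developed to define compliance". No author is named for these criteria.
- A further workshop of key stakeholders is to validate the scoring and "agree on weightings that should be applied to different model components, for each dimension".

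The text after Fig. 2 adds: "All model components will be aggregated by community to develop an implementation fidelity score for each community". Stage 3 then assesses the programme's impact by "looking at the association between the implementation fidelity score and outcome effectiveness".

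**The concern.** The fidelity score is the explanatory variable in Stage 3, and the outcomes it is compared with already exist. Two parts of its definition remain open: how much each component counts, and what counts as compliance. Both rest on judgement. The stated basis for the weights is importance, and views about importance can be coloured by knowing where the programme seemed to work.

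With six communities, a weighted sum of several components is a flexible quantity, and modest changes in the weights can reorder the sites. If those choosing the weights or thresholds know which sites had better HbA1c or fewer admissions, the score can move towards the outcome without any intent to mislead. The article has already put forward implementation failure as a reason for the modest result. An association found with such a score would be read as support for that explanation, and readers could not tell how much of it came from the scoring rule.

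**Working it through.** **Order of events**

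| Step | Status in the article | Where |
|---|---|---|
| Trial outcome data collected, overall result known | Done | Methods/design |
| Measures agreed | Done, May 2015 | Development of measures for implementation fidelity |
| Further compliance criteria | Still to come, author not stated | Scoring model components |
| Weights agreed by stakeholders | Still to come | Scoring model components |
| Community scores formed | After the weights | Text following Fig. 2 |
| Scores related to outcomes | After the scores | Stage 3 |

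The 2015 consensus limits which items are scored. It does not fix their weights or the remaining compliance criteria.

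**Illustration of size**

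The article gives no weights, test, significance level or power, so there is no figure of its own to reproduce.

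From the article: six intervention sites, and one aggregated score per community.

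Assumed: ten components; integer weights 1 to 5; a Pearson correlation between weighted score and outcome; a two-sided 5% test; no true association; at least 4,000 simulated data sets per setting.

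Critical correlation for n = 6: r = t/√(t² + n − 2), with t = 2.776 on 4 degrees of freedom. This gives 2.776/√(7.71 + 4) = 2.776/3.42 = 0.811.

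In each data set, several random weight sets are drawn and the one that correlates best with the outcome is kept. A false positive means the kept set exceeds 0.811.

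| Weight sets tried | Independent, two-sided | Correlation 0.5, two-sided | Independent, favourable only | Correlation 0.5, favourable only |
|---|---|---|---|---|
| 1 (fixed in advance) | 5% | 5% | 2.5% | 2.5% |
| 5 | about 14% | about 8% | about 7% | 3–4% |
| 20 | about 25% | about 10% | about 13% | about 5% |
| 50 | about 32% | about 11% | about 17% | about 6% |

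At correlation 0.3 the two-sided rates for 5, 20 and 50 sets are about 9%, 11–13% and 15%. With independent components, the median best |r| rises from about 0.34 with one set to about 0.55, 0.66 and 0.71.

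A second setting used 4 to 10 independent components, non-negative weights free to be more uneven than 1 to 5, and favourable associations only. The rate went from 2.3–3.0% with one set to 8–9% with the best of 5 and 15–21% with the best of 20. The size therefore depends on how correlated the components are, how uneven the weights may be and how many alternatives are in play. The article states none of these.

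**The case against.** **Site-level knowledge is not shown.** Tuning requires knowing which sites did better. The article reports only that the trial as a whole gave modest results. A reader might infer that workshop members know the site outcomes, or will be shown draft scores because they are asked to validate the scoring. The text says neither. This stands, and it makes the point conditional.

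**Authorship of the criteria.** A reader might infer that stakeholders will also write the compliance criteria. The article gives them the weights and the validation of scoring, and names no author for the criteria. This also stands.

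**Silence in a condensed article.** A lock date, masking or a sensitivity analysis may be in a fuller document, and their absence here is not itself an error. That is fair. The point rests instead on a sequence the article does state: known overall result, then weights and criteria, then comparison with the same trial's outcomes.

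**Existing safeguards.** Measures were agreed in 2015, weights are meant to reflect importance, compliance is to follow a per-protocol approach, and Stage 2 precedes Stage 3. These reduce the freedom available. They do not close it, because the outcome data predate Stage 2, and doing Stage 2 first does not hide them.

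**The illustration is severe.** The article describes one consensus process. The simulation models a deliberate search, and independent components give its largest rates. This is right, and it is why the correlated and favourable-only figures are given.

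**Reach.** A reader might infer that the whole study would lose credibility. The association is one of four objectives. The context findings and the component-level description do not depend on the weights, and Stage 3 also names component scores as the independent variable, where weights between components need not enter. Compliance criteria would still affect those component scores.

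**Conclusion.** The point holds as a conditional risk. The article itself places the setting of weights and further compliance criteria after the trial's overall result and before the comparison with that trial's outcomes. If those setting the rules know the site results, the score can be tuned towards an association. The article does not establish that they do, and nothing in it shows that tuning has occurred or is intended.

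Under the assumptions above (weights 1 to 5, ten components, best of 5 to 50 sets), the two-sided false-positive rate rises from 5% to about 14–32% with independent components and to about 8–11% at correlation 0.5, with about half of that in the favourable direction. For those settings this is an upper bound on what selection could do, because a workshop seeking consensus on importance would not search for the best fit. It is not an estimate of bias here. The consequence is confined to the objective on fidelity and outcomes. A cheap improvement to the plan is warranted.

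**What to change.** Add three statements to Stage 2 and Stage 3:

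1. All compliance criteria and component weights are finalised, dated and locked before any site score is linked to outcomes, and the article names who sets the criteria.
2. The workshop works from component descriptions only, without site-identified scores, HbA1c or hospitalisation results.
3. The Stage 3 association is always reported with equal weights next to the stakeholder-weighted score, as an analysis stated in advance.

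The cost is a lock step and one extra analysis run. Stakeholder input is kept. Some participants may already know how individual sites performed, and masking cannot undo that. Record who knew what, and report it as a limitation.

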**Fig. 2 Fig2:**
[figure not shown]
Directed Acyclic Graph (DAG) - Implementation fidelity GBACC project

A series of excel tables will be generated that shows the raw data and implementation score assigned for each component. All model components will be aggregated by community to develop an implementation fidelity score for each community.

### Stage 3: Assessment of intervention effectiveness

The objective of stage 3 is to assess the impact of the program by looking at the association between the implementation fidelity score and outcome effectiveness. The aim is to determine if it is possible to predict outcome effectiveness based on the features of the PHC system. Intervention effectiveness (i.e implementation fidelity score for each component) is the independent variable and avoidable hospitalisations and service utilisation is the dependent variable.

Figure 3 provides a summary of the study design to assess implementation fidelity of phase 1 of the GBACC study.

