#### Describing the context for primary health care service delivery

A systematic literature review will be completed to identify the features of health services for Indigenous communities that contribute to effective primary health care interventions. The results will be used to develop a questionnaire to collect information about the health service context in the six intervention sites of the GBACC study. The objective of the questionnaire is to understand the management and service delivery support structures in place to support the intervention.

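### Stage 3 calls a non-randomised, community-level association between fidelity score and outcome the impact of the programme, and gives baseline differences and the randomised control communities no role

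*Protocol article*

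**What the plan says.** The Stage 3 section of the Protocol article gives its objective as to "assess the impact of the program by looking at the association between the implementation fidelity score and outcome effectiveness". For the analysis, it states that the "implementation fidelity score for each component) is the independent variable" and that "avoidable hospitalisations and service utilisation is the dependent variable". It names no baseline value, change score, covariate or comparison with control communities.

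The matching objective under Methods/design is more modest and names different outcomes. It concerns "any association between implementation fidelity and health outcomes as measured by HbA1c and preventable hospitalisation for diabetes related conditions for communities in the GBACC study", and claims no more.

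The text below Fig. 2 fixes the unit of the score: "All model components will be aggregated by community to develop an implementation fidelity score for each community". The service-context questionnaire is meant to "collect information about the health service context in the six intervention sites of the GBACC study", and it "will be emailed to the Primary Health Care Manager or equivalent in the intervention sites" (n = 6). Methods/design is wider about the framework as a whole, which the authors intend to "apply it to the communities that participated in phase 1 of the Getting Better at Chronic Care in North Queensland (GBACC) study".

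Methods/design also describes the parent study as a cluster randomised trial whose primary outcome was the reduction in HbA1c over 18 months. It says that the trial's clinical outcome data will be used here.

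**The concern.** The communities were randomised to the intervention or to control. They were not randomised to a level of fidelity. Any gradient of outcome over fidelity score is an observational comparison of communities, made with very few of them.

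The article itself supplies plausible common causes. Its Background lists workforce supply and skills, access to services, information technology and lack of resources as barriers to effective chronic disease interventions. It also names an organisation's capacity to manage change as a predictor of success. A community that does well on these may deliver the model more completely and also have better outcomes for reasons unrelated to the model. The Stage 2 section uses context information to find enablers and barriers to implementation. Neither it nor Stage 3 treats these factors as confounders of the link between fidelity and outcome.

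At stake is how the result will be read. Methods/design says that the parent trial gave modest results and offers implementation failure as a possible reason. If Stage 3 finds a gradient and reports it as impact, readers will conclude that the programme works when properly delivered. If it finds none, they may conclude that the programme does not work. Neither follows from an association across communities. Telling poor delivery from an ineffective programme also needs a reference level without the programme, and Stage 3 names none.

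**Working it through.** The article gives no sample size, power, significance level or effect size for Stage 3, so there is no figure to reproduce. The argument rests on setting the texts side by side; the numbers only illustrate the mechanism.

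**The texts.** Stage 3 speaks of impact, while the objective in Methods/design speaks of association. Stage 3 takes avoidable hospitalisations and service utilisation as the outcome, while the objective takes HbA1c and preventable diabetes-related hospitalisation. The two therefore differ in both the strength of the claim and the outcome.

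**Illustration 1: direction of bias.** All inputs are assumptions. Let F be the fidelity score, B baseline severity and Y the follow-up value, each measured so that lower Y is better. B and Y have equal variance, and F is related to Y only through B, so the true fidelity effect is zero. If less-ill communities achieve higher fidelity, corr(F,B) is negative.

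- Follow-up value: corr(F,Y) = corr(F,B) × corr(B,Y) = -0.5 × 0.7 = -0.35
- Change from baseline: corr(F,Y-B) = corr(F,B) × (corr(B,Y) - 1) / √(2 × (1 - corr(B,Y))) = -0.5 × (-0.3) / √0.6 = +0.19
- Adjusted for B: the numerator of the partial correlation is -0.35 - (-0.5 × 0.7) = 0

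The same formulas over a range:

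| corr(F,B) | corr(B,Y) | Follow-up value | Change |
|---|---|---|---|
| -0.5 | 0.5 | -0.25 | +0.25 |
| -0.5 | 0.7 | -0.35 | +0.19 |
| -0.5 | 0.8 | -0.40 | +0.16 |
| -0.3 | 0.7 | -0.21 | +0.12 |
| -0.7 | 0.7 | -0.49 | +0.27 |

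With no fidelity effect, the follow-up analysis suggests benefit and the change analysis suggests harm. Simply switching to change scores does not solve the problem.

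**Illustration 2: six scores.** Assume one score for each of six sites, normal variables and a two-sided 5% test. The critical correlation is t/√(4 + t²), with t the 97.5% point on 4 degrees of freedom, which gives 0.811. In a simulation of 200,000 replicates, the power to detect a true correlation of 0.3, 0.5, 0.7 or 0.9 is 8%, 17%, 37% and 82%.

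Next, let a case-mix variable have the same correlation with fidelity as with outcome, again with no fidelity effect. The unadjusted false-positive rates are as follows (the test is two-sided, so sign does not matter):

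| Both correlations | 0 | 0.3 | 0.5 | 0.7 | 0.8 | 0.9 |
|---|---|---|---|---|---|---|
| False-positive rate | 5.0% | 5.3% | 7.3% | 16.4% | 29.2% | 58.0% |

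Adjusting for that variable at site level brings the rate back to about 5% throughout. It leaves 3 degrees of freedom, however, and raises the critical partial correlation to 0.878.

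**The case against.** The strongest reply is that this is a condensed article. Covariates and model form are commonly left to a full protocol or analysis plan, and Figs 1 to 3, including the directed acyclic graph and the study-design figure, are not shown. Most of the article speaks of association, and the next sentence of Stage 3 speaks of prediction. The parent trial has already addressed the programme's effect, so Stage 3 need not repeat it.

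Much of this stands, and it rules out stronger readings that a reader might infer:

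- *Stage 3 will use raw follow-up values without baseline adjustment.* The article does not say so. Stage 3 is silent, the parent primary outcome is a reduction, and Methods/design speaks of improvement in clinical measures. Silence on covariates in an article is not an error.
- *Stage 3 data come only from the six intervention sites.* This is documented for the questionnaire alone. It is a reasonable inference for the scores, since fidelity has no natural value where the intervention was not given. But Methods/design refers to the communities in phase 1, and it does not restrict the trial's clinical data by arm.
- *Confounding will produce a false fidelity effect of a known size.* No correlation is given in the article. At 0.3 the false-positive rate hardly moves, and at 0.5 it reaches only 7.3%.

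It is also true that adjustment cannot make fidelity randomised, and that control communities add no information on the fidelity gradient itself.

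The objection does not reach the stated aim. Calling the association the impact of the programme is a claim in the text, not a detail left to another document, and it conflicts with the article's own objective.

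**Conclusion.** The point holds in a limited form. Stage 3 states a programme-impact aim that a non-randomised association across communities cannot meet. It exceeds the objective in Methods/design, names different outcomes from it, and gives no role to baseline differences or to the parent trial's control communities.

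That case-mix and resources can drive both fidelity and outcome follows from the design and from the article's own Background. How far they do so is unknown. The expected correlations of -0.35 and +0.19 rest wholly on assumed correlations of -0.5 and 0.7, equal variances and no other path from fidelity to outcome. If only intervention sites are scored, about six scores carry the whole analysis. Imprecision is then at least as serious as bias, and adjustment alone cannot support a causal reading.

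**What to change.** 1. In Stage 3, replace the impact wording with an exploratory association between fidelity and outcome across intervention communities.
2. Bring the Stage 3 outcomes into line with the objective: HbA1c and preventable diabetes-related hospitalisation. If service utilisation is kept, say what it is for.
3. Estimate the association from the existing patient-level trial data. For HbA1c, use a mixed model with baseline HbA1c as covariate and a random intercept for community. For hospitalisation, use rates with the pre-trial rate as covariate where available. Include both arms, so that the control communities help to supply the baseline slope and provide the reference level, and let the score enter for intervention communities only. Patient-level baseline data avoid spending one of the few site-level degrees of freedom on baseline.
4. State which communities are scored. If only the intervention sites are, state that the fidelity estimate rests on about six scores.
5. State that unmeasured community confounding remains and that no causal conclusion follows.

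The cost is some extra analysis work and a more modest stated conclusion. Methods/design already names the trial's clinical outcome data as a source; access to control-arm and pre-trial records should be confirmed.

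### Stage 3 is inconsistent about which fidelity score is the predictor, and six scored sites support neither component-level inference nor prediction

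*Protocol article*

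**What the plan says.** The objectives under Methods/design ask the investigators to "Assess the level of implementation fidelity achieved for each component of the intervention in each community", so component scores are defined per community. The text below Fig. 2, in the section on scoring model components, goes a step further: "All model components will be aggregated by community to develop an implementation fidelity score for each community". The abstract likewise describes a weighted overall score for each community.

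The opening sentence of Stage 3 relates a single fidelity score to outcome effectiveness. The same paragraph then says "The aim is to determine if it is possible to predict outcome effectiveness based on the features of the PHC system", and fixes the predictor at component level: "Intervention effectiveness (i.e implementation fidelity score for each component) is the independent variable".

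The outcome also differs between sections. In Stage 3, "avoidable hospitalisations and service utilisation is the dependent variable". The objectives instead name "health outcomes as measured by HbA1c and preventable hospitalisation for diabetes related conditions for communities in the GBACC study".

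On the number of units, the context questionnaire covers "the health service context in the six intervention sites of the GBACC study", and the section on that questionnaire repeats n = 6. The text does not give the number of components (Fig. 2 is not shown), and the article states no model, significance level or power.

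**The concern.** A fidelity score belongs to a community. Every patient in a site shares it, so patient-level outcomes cannot add information about how fidelity varies. Six sites give five between-site degrees of freedom in total. Reading the predictor as the score for each component means several predictors share those five.

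Methods/design raises implementation failure as a possible reason for the parent trial's modest results, and Stage 3 is the step that would examine it. A component-level analysis on six sites could credit a component by chance. A null result, at the power available, could be taken to mean that fidelity does not matter. A stated aim of prediction invites both errors.

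**Working it through.** The article gives no sample-size or power figure to reproduce, so the check starts from the design.

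**Inputs**
- n = 6 scored sites (sections on describing the context and on the service context questionnaire).
- k = number of components: not stated; assumed range 3 to 10.
- Outcomes: two in Stage 3 (avoidable hospitalisations, service utilisation).
- Significance level: not stated; two-sided 0.05 assumed.

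**1. All components in one linear model.** Residual df = n − 1 − k = 5 − k. Expected R-squared when nothing is related = k/(n − 1) = k/5.

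| k | Residual df | Expected null R-squared |
|---|---|---|
| 3 | 2 | 0.60 |
| 4 | 1 | 0.80 |
| 5 | 0 | 1.00 (exact fit) |
| 6 or more | none | coefficients not estimable |

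**2. Components tested one at a time.** Chance of at least one false positive = 1 − 0.95^m, with m independent tests.

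| k | One outcome (m = k) | Two outcomes (m = 2k) |
|---|---|---|
| 3 | 14% | 26% |
| 4 | 19% | 34% |
| 5 | 23% | 40% |
| 6 | 26% | 46% |
| 8 | 34% | 56% |
| 10 | 40% | 64% |

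For example, 1 − 0.95^6 = 0.265 and 1 − 0.95^20 = 0.642. Correlated scores lower these figures. Simulation at n = 6 with a correlation of 0.5 between component scores and one outcome gives 17% for k = 4 and 33% for k = 10.

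**3. One predictor, one outcome.** With 4 df, t(0.975) = 2.776, so the critical |r| = 2.776/√(4 + 2.776²) = 0.811.

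For Spearman at n = 6, rho = 1 − Σd²/35. Of the 720 orderings, 1, 5 and 6 have Σd² of 0, 2 and 4. Counting both tails, |rho| ≥ 1 − 4/35 = 0.886 has probability 2 × 12/720 = 0.033. The next value, 1 − 6/35 = 0.829, adds 9 orderings and gives 2 × 21/720 = 0.058, which is not significant.

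Simulated power of one Pearson correlation (200,000 bivariate normal draws, n = 6):

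| True r | Power |
|---|---|
| 0.5 | 17% |
| 0.7 | 37% |
| 0.8 | 56% |
| 0.9 | 82% |

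An observed r of 0.5 has a Fisher-z 95% interval of tanh(0.549 ± 1.96/√3), that is −0.52 to 0.93.

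**The case against.** The best reply is that the article commits to none of the analyses calculated here. It speaks only of association; joint regression, component-by-component tests and a 5% level are nowhere written, and such choices are commonly left to an analysis plan. A descriptive comparison would fit the text equally well. This stands. A reader might infer that Stage 3 will fit a saturated model or run many tests, but the documents do not support that, and the figures show only what would follow if it did.

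Three other strong readings also fail:
- **That Stage 3 abandons the overall score.** Its opening sentence uses a single score, so the text is inconsistent rather than committed to components alone.
- **That outcomes are to be predicted from component scores.** The predictive sentence refers to features of the primary health care system, which the context questionnaire captures as enablers and barriers. Those features are also known for only six sites, so the limit is the same.
- **That saturation or a 64% error rate is established.** Exact fit needs at least five components, and 64% is the top of an assumed range.

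It is also fair to say that the single-predictor figures apply unchanged to the remedy, and that this is a secondary study developing a method. Both points bear on severity.

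The reply does not remove the limit on units. The article itself fixes the level of the predictor and the predictive aim, and no analysis plan can create more scored sites. The article gives control communities no fidelity score, so they do not clearly add units.

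**Conclusion.** The point holds in a limited form and should be fixed. Stage 3 contradicts itself on whether the predictor is one score or one per component. The component reading cannot support inference with six sites: a joint model is near-saturated with three or four components, saturated with five and not estimable beyond that. Separate tests on two outcomes would carry a 26% to 64% chance of a false positive. Prediction is out of reach even with one predictor, since 80% power needs a true correlation of about 0.9.

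This rests on six scored sites, which the article supports, and on 3 to 10 components, a two-sided 5% level and independent tests, which are assumptions. The inconsistency and the limit of five between-site degrees of freedom depend on none of those assumptions about components or testing.

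**What to change.** Rewrite the Stage 3 paragraph as follows.
- **Predictor and outcome.** Name the overall community score, already defined in the abstract and in the section on scoring model components, as the one predictor of one outcome chosen in advance. First reconcile the objectives (HbA1c and preventable hospitalisation) with Stage 3 (avoidable hospitalisations and service utilisation). The investigators must make that choice; the point does not depend on it.
- **Analysis.** Work at community level. Report an estimate, a 95% confidence interval and an exact permutation p-value.
- **Components and context.** Show component scores and health-system features descriptively, for example in a site-by-component table beside the questionnaire findings, without significance tests.
- **Claim.** Replace the predictive aim with one of estimating and describing the association, labelled hypothesis-generating, and state that a wide interval is not evidence of no association.

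The cost is wording, a more modest claim and no formal inference on components. No new data are needed. Low power remains after the change, which is why the predictive language has to go as well.
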